# A counselling intervention for individual strategies to prevent complications and strengthen resources during pregnancy in gynaecological care (AOK-Family +): study protocol for a cluster-randomised controlled trial

**DOI:** 10.1186/s13063-024-08215-5

**Published:** 2024-06-18

**Keywords:** Pregnancy, Health knowledge, Health behaviours, Prevention, Health literacy

## Abstract

**Background:**

Lifestyle-related risk factors can increase complications during pregnancy and negatively impact the health of a mother and her child. Knowledge about these compliances among many pregnant women and women of childbearing age is lacking. In the study AOK-Family + , we propose the evaluation of a newly developed counselling intervention. The intervention aims to raise awareness and to provide relevant information about the impact of lifestyle-related risk factors during pregnancy. The aim of the proposed study is to evaluate the effect of this counselling intervention on women’s knowledge of lifestyle-related risk factors during pregnancy and the concomitant healthy behaviours.

**Methods:**

A cluster-randomised trial with three arms in Baden-Wuerttemberg, Germany, is proposed. Pregnant women and women of childbearing age will be allocated to one of three groups: online intervention, on-site intervention, or a waiting-list control. Trained counsellors from AOK Baden-Wuerttemberg, a German statutory health insurer, will conduct the counselling sessions. Data collection is conducted throughout validated questionnaires administered at three intervals: before counselling (*t*0), directly after counselling (*t*1), and at a 6-week follow-up (*t*2). The primary outcomes will be health knowledge and healthy behaviours relating to LRFFs during pregnancy. A process evaluation will examine the processes, used resources, and future implementations through additional quantitative questions and qualitative interviews and focus groups.

**Discussion:**

Based on this study, an implementation strategy for future conduction of lifestyle consultation during pregnancy could be developed with the aim of reducing pre- and post-mortem mobility and mortality.

**Trial registration:**

The German Clinical Trials Register DRKS00027804. Registered on 2022/01/12.

**Supplementary Information:**

The online version contains supplementary material available at 10.1186/s13063-024-08215-5.

## Background

### Background and rationale

Non-communicable diseases (NCDs) account for more than 60% of the global burden of disease [1]. In 2019, 41 million deaths worldwide were caused by NCDs [2]. They are the leading cause of death among women in Germany: 93.3% of all deaths among women are from NCDs, of which 40.7% are from cardiovascular disease [3]. According to the World Health Organization (WHO), these NCDs are linked to four modifiable risk factors: physical inactivity, an unbalanced diet, the consumption of tobacco, and the consumption of alcohol. The WHO defines these as lifestyle-related risk factors (LRRFs) [2]. In Germany, statutory health insurers are obligated to provide primary prevention services according to the law (§§20, 20a, 20b, 20c SGB V), including services dedicated to the prevention of disease and promotion of healthy behaviours in five key lifestyle areas: physical activity, nutrition, stress management, resource management, and substance use [4].

The unhealthy lifestyle behaviours people adopt are highlighted during particular life phases, such as pregnancy. Previous studies in Germany have shown that, for instance, 10.9% of mothers smoked during pregnancy [5] and 14% occasionally consumed alcohol [6]. Additionally, 21.9% of mothers were overweight at the beginning of pregnancy and 14.7% were obese [7]. A recent survey of pregnant women in Germany found that 31.8% did not know the adverse health effects of alcohol consumption during pregnancy. Comparably, 48.5% underestimated the negative effects of smoking tobacco during pregnancy. In addition, 70.8% did not know the composition of a healthy diet according to recommendations [8]. Interestingly, health care providers do not provide a standardised form of education regarding the impact of LRRFs on pregnancy and lactation [9]. Despite the evidence that inadequate health literacy is associated with smoking, a lack of conviction regarding medication, a lack of adherence, and increased risk perception, as well as the fact that strengthened health literacy can improve health and health behaviours during pregnancy, there are only a few routine health care programmes aimed at improving health literacy among pregnant women in Germany [10]. In line with this recognised research gap regarding the effects of counselling and information on birth-related topics, the National Health Goal “Health around Childbirth” calls for measures to improve the delivery of care with regard to LRRFs during pregnancy [11].

### Objectives

The AOK-Family + trial aims to evaluate the effects of online and on-site counselling interventions conducted at health centres by the statutory health insurer AOK Baden-Wuerttemberg. The intervention intends to raise the awareness of LRRFs and healthy behaviours relating to pregnancy, and its implementation in a counselling context as a service provided by a statutory health insurer has not, to our best knowledge, been tested before. The aim of the proposed study is to assess the effect of a lifestyle-oriented counselling intervention on pregnancy-related health literacy in terms of knowledge and healthy behaviours. In addition, the effects of the on-site and online interventions will be compared. The study will identify what effects, if any, occur. As the counselling context has not yet been tested as a service of the statutory health insurance and the intervention is being applied for the first time, the study has partly an exploratory character. Nevertheless, statistical testing was set up with a focus on the superiority of the intervention. Finally, the delivery of the interventions will be documented and evaluated. In addition, an accompanying process evaluation will be conducted in which client satisfaction, user-friendliness, practicability and the process flow will be assessed on the one hand, and the target group, the role perception of the counsellors as well as the positioning of the counselling within the German health care system will be examined on the other hand.

## Methods

### Study design and setting

A cluster-randomised longitudinal three-armed trial is proposed. Participants in the first study arm will receive an on-site counselling intervention, study arm two will receive an online counselling intervention, while those in study arm three comprise a waiting-list control group. Participants in the control group will be able to receive the consultation after data collection. The newly developed counselling intervention will address the relationship between LRRFs and pregnancy, covering information on nutrition, physical activity, relaxation, stress management, and substance use during pregnancy. This study will be accompanied by a process evaluation; further details are provided in the related sections. For the development of the study protocol, the standard protocol items of the recommendations for interventional trails (SPIRIT) [12] were used. Possible changes to the procedure will be communicated to all relevant groups such as investigators, funder, study registry and AOK Baden-Wuerttemberg employees. No audit of the trial is planned.

### Study population and counsellors

The target group will include pregnant women and women of childbearing age who are between 18 and 49 years, able to give consent and insured with AOK Baden-Wuerttemberg. The ability to read and understand German is a requirement for participation.

The study counsellors will be AOK Baden-Wuerttemberg employees who have completed a degree in nutrition or sports science and have experience with LRRF counselling. They will complete a standardised training in advance.

### Recruitment of study participants

Participants are made aware of the study with the help of flyers in waiting rooms of gynaecological practices. In addition, further advertisements will be placed via health insurance company advertising channels (e.g. social media and insurance magazines). Interested participants can then contact AOK Baden-Wuerttemberg by phone. After participating in the study, all participants will receive an incentive. The incentive is a voucher code for the e-book “Handbook of Family Health” [13] with a value of EUR 12,99.

### Randomisation process

The 14 district directorates of AOK Baden-Wuerttemberg (Fig. 1), in Southwest Germany, are randomly assigned to one of the three study groups: the on-site intervention group, the online intervention group, or the control group. The initial randomisation process has been performed via computer generation and was carried out using a simple cluster-randomised design before the process of enrolment. The cluster randomisation will be conducted by an independent operator using the statistical program R (Version 1.3.5) with the randomizr package. The conduct of randomisation was concealed to the members of the study team. Similarly, the counsellors will be allocated according to their place of employment. Depending on where the insured people live, they will be assigned to the appropriate district directorate (e.g. if an insured person lives in the Ludwigsburg-Boeblingen area, she will be assigned to the Ludwigsburg-Boeblingen district directorate and the staff employed there). If an insured person is interested in the study, she will receive the intervention assigned to the responsible district directorate (e.g. insured person lives in the Ludwigsburg-Boeblingen area. The area has been assigned to intervention arm 1. The insured person is therefore automatically assigned to intervention arm 1). This means that the district directorates should be considered as randomised units.

**Fig. 1 Fig1:**
[figure not shown]
AOK Baden-Wuerttemberg district directorates

### Assignment of interventions

Those interested in the study will be invited to contact AOK Baden-Wuerttemberg by phone to receive information on participation in the study from a trained staff member. As already mentioned, the participants were assigned to the intervention, which was randomly allocated to their district directorates. In the course of the telephone call, interested participants also receive information about the study arm to which their responsible district directorate has been assigned. Participants may stop the session at any point if they wish. There are no specific measures to increase adherence (e.g. to ensure participants attend and complete their session). Because this is a one-off session, the likelihood of patients stopping the session early was felt to be limited.

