### Interventions

The interventions are educational, aiming to increase the awareness of LRRFs during pregnancy and the concomitant healthy behaviours supporting women. To achieve this, the interventions address LRRFs related to nutrition, physical activity, relaxation, stress management, and substance use for a planned period of 6 months. If in the course of counselling the need for further support services (e.g. nutrition counselling) is identified, the counsellor refers to the corresponding services. However, these are not part of the intervention. There were no restrictions on concomitant care. Overall, there is no blinding (including study participants) for the intervention. No possible harm data is collected. Termination of the study will be made by the study director. The SPIRIT [12] and TIDieR checklist [14] were used for the preparation of the intervention (see the Supplementary Materials). Table 1 shows the SPIRIT figure.

**Table 1 Tab1:** Enrolment, intervention and assessments of the “AOK-Family + ”

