### Participant timeline, data collection, and management

Following verbal informed consent, a consultation appointment will be arranged for the intervention groups, and the participants will receive access (QR-Code and URL) to the first online questionnaire (*t*0), which will also be posted by mail. Verbal informed consent is recorded by the project team of AOK Baden-Wuerttemberg. Before starting the questionnaire, the participants’ consent is obtained again by actively ticking a checkbox. This baseline questionnaire should be answered up to 24 h before the counselling session (duration approximately 20–30 min) and will capture their socio-demographic data, health knowledge, and health-related behaviours. At the appointment, before the start of the counselling session, the participants will be asked whether the baseline questionnaire (*t*0) has already been completed. If not, completion of the questionnaire will be requested prior to counselling. Otherwise, the counselling intervention (on-site/digital) will take place and will last for approximately 45 min. Immediately after counselling, the counsellors will provide participants with access (QR-Code and URL) to the second online questionnaire (*t*1) to measure the short-term effect of the counselling on health knowledge, together with information regarding client satisfaction and the user-friendliness of the counselling (secondary outcomes) (duration 10 min). This questionnaire should be completed directly after counselling at the health centres or after leaving the digital room.

To measure the longer-term effects of the counselling, a follow-up questionnaire 6 weeks after *t*0 will be conducted, including participants’ health knowledge and healthy behaviours (*t*2), as well as their perceived user-friendliness and client satisfaction (duration approximately 30–35 min). The participants will receive access (QR-Code and URL) to the last online questionnaire by mail.

The waiting-list control group will receive access (QR-Code and URL) to the baseline questionnaire after they gave consent for study participation and receive the last questionnaire (*t*2) 6 weeks later by mail. After completion of the follow-up survey, the participants in the control group can individually arrange a requested AOK-Family + consultation. Table 3 summarises the timing and content of the questionnaires for each study arm.

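### Callers learn their arm before baseline and only the counselling arms have a t0 check, so women can join selectively by arm; the stated primary model adjusts only for t0 outcome values

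*Protocol article*

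**What the plan says.** **Order of events.** According to Randomisation process, allocation of the 14 directorates "was carried out using a simple cluster-randomised design before the process of enrolment", and a woman's residence then fixes her arm. Under Assignment of interventions, women who phone the insurer are informed by a trained staff member, and in that call "interested participants also receive information about the study arm to which their responsible district directorate has been assigned".

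**Concealment and blinding.** Randomisation process states: "The conduct of randomisation was concealed to the members of the study team". Interventions states: "Overall, there is no blinding (including study participants) for the intervention".

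**Consent and t0.** Participant timeline, data collection, and management says: "Following verbal informed consent, a consultation appointment will be arranged for the intervention groups". Access to t0 is given at this stage, and later "Before starting the questionnaire, the participants’ consent is obtained again by actively ticking a checkbox".

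**Handling of t0 by arm.** At the counselling appointment, women are asked whether t0 is done: "If not, completion of the questionnaire will be requested prior to counselling". The same section adds that counselling starts only once t0 is complete. For controls it says: "The waiting-list control group will receive access (QR-Code and URL) to the baseline questionnaire after they gave consent for study participation". The footnote to Table 1 asks them to answer soon after receipt, without a limit.

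**Primary model.** Statistical analysis, Primary outcomes, compares both counselling arms with control at t2, adjusted for t0 values of the primary outcomes, with random coefficients for directorates. It presents this as the way to control baseline differences and names no other covariate. Socioeconomic factors, previous pregnancies, number of children and previous counselling appear only under Other exploratory analysis.

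**The concern.** Randomising directorates balances directorates in expectation. It does not balance who volunteers within them when volunteers already know what they will get. The three offers differ visibly: a visit to a health centre, an online session, or a wait of about six weeks. Women who accept the wait may differ in motivation, education or prior knowledge from those who accept immediate counselling.

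Concealing the conduct of randomisation from the study team does not conceal the allocation from the caller or from the staff member who tells her.

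The unequal handling of t0 adds a second filter. A woman in a counselling arm who arrives without t0 is asked to complete it before she is counselled. A control who leaves the link unopened meets no described check or t0 reminder, and because enrolment is counted at t0 she never enters the enrolled sample.

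At stake are both co-primary comparisons with control. A selection difference would be read as an effect of counselling, or would mask one, and the stated adjustment removes only the part that the t0 outcome values capture.

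**Working it through.** **1. Sequence, passage against passage**

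| Step | Counselling arms | Control arm |
|---|---|---|
| Directorate randomised | before enrolment | before enrolment |
| Arm disclosed | on the recruiting call | on the recruiting call |
| Verbal consent | order against disclosure not stated | order against disclosure not stated |
| t0 access | after verbal consent | after verbal consent |
| Second consent | checkbox when the questionnaire is opened | same |
| Check on t0 | asked at the appointment; counselling waits for it | none described |

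Disclosure precedes t0 and the checkbox consent in every arm. That follows from the text and is enough for the selection argument.

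**2. The plan's own sample size**

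- Inputs (Sample size calculation): 50% against 65%, power 65%, two-sided alpha 5%, ICC 0.01, about 36 women per cluster.
- Design effect = 1 + (36 − 1) × 0.01 = 1.35.
- Standardised difference = 0.15 / 0.5 = 0.30. A two-sample t-test needs 123.2, so 124 per arm.
- 124 × 1.35 = 167.4, so 168 per arm. This matches the plan.
- Enrolment: 504 / 0.8 = 630, against 638 stated, within 3%.

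No change to the sample size follows from this point.

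**3. Illustration in SD units (the bias is assumed)**

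- SE of an arm contrast = √(2 × 1.35 / 168) = 0.127 SD.
- With residual bias b and no true effect, the test statistic is shifted by b / 0.127.
- t reference: 14 directorates − 3 arms = 11 df.

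| Assumed b | Shift | False-positive rate, normal | False-positive rate, t with 11 df |
|---|---|---|---|
| 0 | 0 | 5% | 5% |
| 0.1 SD | 0.79 | 12.4% | 11.2% |
| 0.2 SD | 1.58 | 35.1% | 30.2% |

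**4. Illustration in percentage points (inputs assumed, before any adjustment)**

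Suppose the share of motivated women differs between arms by 10 to 30 points, and their success rate is 10 to 30 points higher. The shift is the product of the two.

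- Smallest: 0.10 × 0.10 = 1 point. Middle: 0.20 × 0.20 = 4 points. Largest: 0.30 × 0.30 = 9 points. The planned effect is 15 points.
- SE = √(2 × 0.25 / (168 / 1.35)) = 0.0634.
- Rejection rate under no true effect (normal): 5.3%, 9.7% and 29.5%.

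Adjustment for t0 would reduce these by an amount the documents do not let one compute.

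**The case against.** **Consent.** A reader might infer that the arm is disclosed before any consent. The protocol says only that both belong to the phone contact. Table 1 even puts informed consent in a column ahead of allocation, although both carry the same time label and Randomisation process places randomisation before enrolment. Disclosure before verbal consent is plausible but not stated, and the point does not need it.

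**Knowledge as self-report.** A reader might treat both baselines as equally open to distortion by knowledge of the arm. The knowledge survey is a test scored against guidelines, so adjusting for it handles selection on knowledge level reasonably well. The concern about a baseline answered with the arm known applies mainly to reported behaviour.

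**Controls have reasons to complete.** The voucher depends on full participation in all arms, and controls are offered counselling after t2. This softens the unequal check on t0 without removing it. The documents contain no evidence that completion actually differs by arm.

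**The analysis plan may add covariates.** It may, and it is not shown. But the protocol does state a primary model and offers baseline adjustment as the remedy for imbalance, while placing the relevant characteristics in exploratory work. No analysis plan can undo the recruitment order.

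**The size is invented.** The bias inputs are assumptions, no direction is established, and the lower end of the range is close to nominal. This stands: the figures show sensitivity and do not show that the trial is biased.

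**Conclusion.** The point holds as a risk built into the design. Allocation precedes enrolment, the arm is known before t0 and before the checkbox consent, and only the counselling arms have a check on t0. The stated primary model adjusts for nothing beyond t0 outcome values. Selective joining or selective t0 completion can therefore bias both comparisons with control, and the limitations in the Discussion do not mention it.

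Its size is unknown. The rates of about 11–12% at 0.1 SD and 30–35% at 0.2 SD rest on assumed residual bias, together with the plan's 168 per arm and design effect of 1.35. They should not be quoted as the trial's error rate. The documents do not support saying that the arms do differ, or in which direction.

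**What to change.** **Analysis (still available).** In Statistical analysis, Primary outcomes, add to the model for both outcomes the fixed characteristics collected at t0: age, education, occupation, household income and country of birth. Add number of previous pregnancies, number of children and previous lifestyle counselling if these are recorded at t0; the protocol names them for exploratory analysis without saying when they are collected. Pregnancy status is not listed as a collected item, so it cannot be assumed available.

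**Reporting.** Give consenters and t0 completers per directorate and arm, and name recruitment after disclosure as a limitation in the Discussion.

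**Cost.** A few more model parameters and some wording. Unmeasured motivation is not removed.

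**Prevention.** Taking consent and t0 before disclosing the arm would avoid the problem. However, this protocol version is dated 11 June 2024 and recruitment, begun on 24 April 2023, ends on 30 June 2024. The change could reach at most the last 19 days of recruitment, or a later trial. It would also need a second contact to book the appointment and might lose some callers once they learn they must wait. It would have to be reconciled with the rule tying t0 to the appointment, and with t2 being counted from t0.

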### Interventions

The interventions are educational, aiming to increase the awareness of LRRFs during pregnancy and the concomitant healthy behaviours supporting women. To achieve this, the interventions address LRRFs related to nutrition, physical activity, relaxation, stress management, and substance use for a planned period of 6 months. If in the course of counselling the need for further support services (e.g. nutrition counselling) is identified, the counsellor refers to the corresponding services. However, these are not part of the intervention. There were no restrictions on concomitant care. Overall, there is no blinding (including study participants) for the intervention. No possible harm data is collected. Termination of the study will be made by the study director. The SPIRIT [12] and TIDieR checklist [14] were used for the preparation of the intervention (see the Supplementary Materials). Table 1 shows the SPIRIT figure.

**Table 1 Tab1:** Enrolment, intervention and assessments of the “AOK-Family + ”

